#### Interviews with stakeholders

To integrate the perspective of those responsible for and involved in the implementation of the IUDPs, we will conduct semi-structured interviews with local stakeholders. Interviewees will include both stakeholders responsible for implementing the IUDP and stakeholders who are either directly involved in implementing the measures on-site or are actively engaged in the development of the district in other ways. Due to the different stages of the IUDP processes in the three intervention areas, the interviews will take place at different times across the study sites: In Wuppertal, interviews will be conducted in the first, following those in Bochum in the second and in Bremen in the third project year.

For the recruitment process, a list of key stakeholders will be compiled. If additional relevant stakeholders are identified during the interview phase, these will be added to the interviews. Individuals will be contacted via email and provided with study information outlining the project’s purpose as well as objectives and data protection procedures. Prior to participation in the interview, all participants will be required to provide written informed consent.

The qualitative interviews address success factors and barriers of IUDPs with regard to ecological sustainability, social equity, and health. A semi-structured interview guide will serve as the basis for the interviews, organised chronologically according to the phases of the IUDP. The guide can be adjusted after each interview in terms of refining questions that have proven difficult or redundant.

Interviews will be conducted either in person or online and will be recorded. In case of online interviews, ZOOM will be used for both conducting and recording the sessions. The recordings will be transcribed automatically using the software noScribe (for more information: https://imt.uni-paderborn.de/software/noscribe).

#### Focus groups with residents

The perspective of the residents, as main target group of the IUDPs, is crucial for evaluating the impacts and processes. We will conduct twelve focus groups, four in each intervention area, to explore how the residents perceive and assess the IUDP process [26]. Participants will be purposively recruited from population groups that are considered particularly vulnerable due to living in relative poverty and are often overlooked in qualitative data collection. Each focus group will address the perspective of one of the following groups: adolescents, elderly, migrants from specific origin countries and communities, and people with disabilities. The focus groups will be conducted in the second year of the project in all three intervention areas.

#### Accelerometery

During both surveys, participants from I1 and C1 will be asked to participate in an accelerometer assessment on physical activity and sleep. Both will be assessed using an ActiGraph wGT3X-BT accelerometer (ActiGraph LLC, Pensacola, FL, USA), worn by participants on the non-dominant wrist 24 h for seven consecutive days. The device measures acceleration and deceleration of the body in three axes [27]. Sampling frequency will be set to 30 Hz. For downloading and pre-processing the measurement data, ActiLife (Version 6.15.0 ActiGraph LLC, Pensacola, FL, USA) will be used. Wear time periods will be determined based on the algorithm by Troiano et al. [28], with 60 consecutive minutes of zero counts defining non-wear time. For sleep, the Cole-Kripke scoring algorithm will be used to identify sleep and wake epochs [29]. Planned indicators are average daily counts per minute, daily minutes in moderate-to-vigorous physical activity (MVPA), total sleep time, sleep efficiency, and wake after sleep onset (WASO).

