Qualitative data from semi-structured interviews and focus groups will be analysed using the method of qualitative content analysis as described by Kuckartz and Rädiker [42]. Unlike Mayring’s approach [43], this method allows not only category-based but also case-based analysis. For the present study, the content-structuring variant of content analysis will be applied [42]. The aim is to systematically structure the material by content. Data analysis will be conducted using MAXQDA software. To ensure quality of the coding process, the recommendations of Kuckartz and Rädiker [42] regarding intercoder agreement will be followed. Previous to the initial coding round, the main categories will be jointly defined by the study team and the interviews will then be independently coded by two team members using these main categories. During this process, the coders will record open questions and ideas for modifying the code tree. Afterwards, the two team members will compare their codes, agree on a consolidated version, and document this in the codebook. In addition, the identification of themes and subthemes will be discussed and agreed upon within the entire study team.

Accelerometer data will be processed using ActiLife software (ActiGraph, Pensacola, FL). Non-wear times will be defined based on the Troiano algorithm [28]. Acceleration measurements across three axes will be aggregated into vector magnitudes and expressed as average counts per minute. Minimum wear time is defined as 22 h per day on at least five consecutive days. Sleep scoring will be conducted according to algorithms developed by Cole and Kripke [29].

Access to study data will be restricted to members of the study team, and data storage will comply with applicable legal regulations.

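### Accelerometer sub-assessment: the 60-minute zero-count non-wear rule has no stated sleep exemption, and the 22 h on five consecutive days criterion can exclude compliant wearers and people with five or six valid days

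*Protocol article*

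**What the plan says.** Under Accelerometery, the device is "worn by participants on the non-dominant wrist 24 h for seven consecutive days". Wear periods follow a published algorithm, "with 60 consecutive minutes of zero counts defining non-wear time". For sleep, "the Cole-Kripke scoring algorithm will be used to identify sleep and wake epochs". The planned indicators are counts per minute, MVPA, total sleep time, sleep efficiency and WASO. Scope is limited: "participants from I1 and C1 will be asked to participate in an accelerometer assessment on physical activity and sleep", so the other two cities are not involved.

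Under Data analyses, the non-wear rule is repeated without modification ("Non-wear times will be defined based on the Troiano algorithm"), the three axes are combined ("Acceleration measurements across three axes will be aggregated into vector magnitudes and expressed as average counts per minute"), and the validity criterion is set: "Minimum wear time is defined as 22 h per day on at least five consecutive days".

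Neither section exempts sleep from the non-wear rule, mentions a sleep diary or in-bed window, or says whether sleep is scored before or after non-wear is removed. Neither gives a reason for requiring consecutive days, or an expected exclusion rate.

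**The concern.** There are two separate problems, both in rules that the article itself fixes.

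First, absence of movement on the same device has two readings. The sleep algorithm reads it as sleep; the wear rule reads it as non-wear once it has lasted 60 minutes. The plan does not say which prevails. Because a day needs 22 h of wear, genuine removals and misclassified sleep share one small daily allowance, and a fully compliant wearer can lose a day.

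Second, a run of five valid days within a seven-day recording is much stricter than five valid days. One bad day in the middle of the week discards an otherwise complete record.

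Records are hard to obtain. Under Recruitment of the participants, volunteers must contact the team themselves and are then visited at home. A participant excluded by a processing rule is an avoidable loss in a sub-assessment confined to one pair of areas.

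**Working it through.** The article states no sample size or expected valid-wear rate for accelerometry, so there is no figure to reproduce. The check uses four stated inputs: 24 h wear, seven days, a 60-minute zero-count threshold, and 22 h on at least five consecutive days.

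**1. Daily allowance.** 24 h − 22 h = 2 h = 120 minutes.

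- No real removal: two flagged bouts of exactly 60 minutes leave 22 h and the day passes. It fails with three 60-minute bouts, two bouts totalling more than 120 minutes, or one bout longer than 120 minutes.
- One real 60-minute removal: a single flagged sleep bout longer than 60 minutes, or two of 60 minutes, fails the day.

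**2. Which single bad day excludes.** If day d of 7 fails, the longest remaining run is max(d − 1, 7 − d). This is 6, 5, 4, 3, 4, 5, 6 for d = 1 to 7. A bad day on day 3, 4 or 5 leaves fewer than five in a row: 3 of the 7 patterns with six valid days (43%).

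**3. Exactly five valid days.** There are C(7,5) = 21 patterns. Only days 1–5, 2–6 and 3–7 are consecutive, so 18 of 21 (86%) are excluded. These percentages are shares of patterns, not of participants.

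**4. Retention.** Assume each day is independently valid with probability p. A qualifying run starts on day 1 (p⁵), or on day 2 or 3 after a failed day ((1 − p)p⁵ each):

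P(run of at least 5) = p⁵[1 + 2(1 − p)]

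P(any 5 of 7) = 21p⁵(1 − p)² + 7p⁶(1 − p) + p⁷

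| p (assumed) | Five consecutive | Any five of seven |
|---|---|---|
| 0.90 | 0.5905 × 1.2 = 70.9% | 97.4% |
| 0.85 | 0.4437 × 1.3 = 57.7% | 92.6% |
| 0.80 | 0.3277 × 1.4 = 45.9% | 85.2% |

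**5. Compliant wearers under the non-wear rule.** Assume no real removal and a Poisson number of flagged still-sleep bouts per night with mean λ. With 75-minute bouts, one fits the allowance and two (150 minutes) do not, so P(day valid) = e^(−λ)(1 + λ). That value is used as p in step 4. With bouts of exactly 60 minutes, two fit, so P(day valid) = e^(−λ)(1 + λ + λ²/2).

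| λ (assumed) | Day valid, 75 min | Participant retained, 75 min | Participant retained, 60 min |
|---|---|---|---|
| 0.1 | 0.995 | 98.6% | 100.0% |
| 0.25 | 0.974 | 92.1% | 99.4% |
| 0.5 | 0.910 | 73.6% | 95.7% |
| 1.0 | 0.736 | 33.0% | 76.4% |

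With 75-minute bouts, exclusion of people who never took the device off runs from 1.4% to 67.0%. With 60-minute bouts it runs from practically nil to 23.6%. The result depends on a rate and a bout length that the documents do not give.

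**The case against.** The strongest reply is that the sleep part rests on an undocumented premise. Nothing in the article says how often 60-minute runs of zero counts occur in sleep at the wrist, and one or two 60-minute bouts alone do not fail a day. That stands: the effect is possible under the rule as written, but its frequency is unknown.

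A reader might infer that still sleep is deleted from the sleep indicators, so that sleep time and efficiency come out too low. The text does not say so. It lists non-wear detection and sleep scoring as separate steps and leaves their order open, which the full protocol or SAP may settle. Nor does it state the denominator for counts per minute, so an upward bias there cannot be asserted either.

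A reader might also infer that sound sleepers are preferentially lost and that the I1–C1 contrast is biased. The same rule applies in both areas at both surveys, and the analysis is difference-in-differences, so constant misclassification would largely cancel. Bias needs still sleep, and hence exclusion, to change differently in the two areas. That is possible, but the documents neither show nor quantify it.

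The consecutive-days rule is explicit and uniform, and the retention figures assume independent days. If bad days sit together or at the ends of the week, more people are kept; if they fall mid-week, fewer. This limits the precision of the figures. It does not touch the pattern counts in steps 2 and 3 or supply a reason for the rule.

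Finally, a weekday-only valid run is possible only when recording starts on a Saturday, Sunday or Monday, and five days is an inclusion threshold rather than a limit on the days analysed. A weekend-day requirement is therefore optional.

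**Conclusion.** The point holds in conditional form and should be settled before accelerometer data are processed. As written, the non-wear rule has no sleep exemption in a 24 h protocol that measures sleep, and the tolerance is 120 minutes a day. Still sleep can therefore be classed as non-wear and can exclude compliant wearers. The 1% to 67% range rests on assumed 75-minute bouts at 0.1 to 1.0 per night with no real removal, and is an illustration rather than an estimate. Sleep time would be understated only if flagged minutes are also taken out of sleep scoring, which is not stated.

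The consecutive-days problem is firmer. The pattern counts (3 of 7 and 18 of 21) follow from the stated rule alone. The retention loss of about 27, 35 and 39 percentage points at p = 0.90, 0.85 and 0.80 needs the independence assumption and the assumed p.

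The consequences are confined to the opt-in I1/C1 assessment. The Outcomes section does not name the accelerometer indicators, and active mobility there is self-reported, so the survey-based conclusions are unaffected.

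**What to change.** - Score the sleep period first, by a stated method, and apply the 60-minute zero-count rule only outside it, so that motionless sleep counts as wear. State this order of steps.
- Replace five consecutive days with any five valid days of the seven.
- Keep the published rule (zero-count non-wear at all hours, 22 h on five consecutive days) as a sensitivity analysis, and report by area and survey how many records each rule excludes.

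The cost is processing settings and wording; no new data are needed. The downside is that some true night-time removals will be counted as wear.

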#### Participatory formats

To ensure meaningful integration of the residents’ perspectives into the evaluation process, we will actively involve them in different participatory formats. Residents will be directly approached and invited to take part in small-group activities that combine observation, discussion, and reflection. Examples include guided neighbourhood walks, during which participants explore their surroundings together and discuss ongoing changes, challenges, and potentials within the urban development process. During these neighbourhood walks, we will use photovoice to document participants’ gaze, capturing what draws their attention in the neighbourhood [30]. We will encourage them to take photos to document their lived experience, helping to reflect on and communicate what matters most to them in their local environment. In addition, meetings will be held at specific sites where IUDP interventions are planned, currently underway, or already completed. These discussions will focus on how residents perceive and use these spaces, what expectations and needs they associate with them, and how the interventions affect their everyday life.

#### Assessment of urban green

Based on Bläser et al. [31] and the German Federal Agency for Nature Conservation [32], we will assess urban green spaces with regard to quality of life and neighbourhood liveability, and examine how the IUDP contributes to socio-ecological transformation. With a focus on flora, the assessment applies specific criteria addressing the quality of flora within this transformation context. This includes mapping ecological indicators such as key plant species, invasive versus native species, and species of particular conservation concern – where possible fauna will be included. Data will be collected along representative circular walking routes that include comparable urban features (e.g., schools, playgrounds, parks) and intervention areas, sites affected by IUDP measures. The approach enables a systematic comparison of urban green quality and its relevance for socio-ecological transformation across all study areas.

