## Methods

### Study setting

This study will evaluate the impact and process quality of IUDPs in three urban areas in Germany. The intervention areas are the districts of Blumenthal (I1) in the city of Bremen, federal state of Bremen in northern Germany, Wattenscheid-Mitte (I2) in Bochum and Mirke (I3) in Wuppertal, both cities located in the federal state of North Rhine-Westphalia in the western part of Germany. In each city, a further district will serve as control area in which no IUDP will be implemented. These control areas are Bremen Kirchhuchting (C1), Bochum Hofstede (C2) and Wuppertal Rott (C3). For the localisation of all six study areas within Germany and the respective cities, see Fig. 1.

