#### IUDP 1 (Bremen)

In Bremen Blumenthal, the IUDP was launched in 2023 with the aim of revitalising the historic district and creating healthier, more equitable living environments. The programme combines spatial, social, and physical environmental interventions to address long-standing challenges of structural inequality and urban neglect.

A significant contextual development is the construction of a new vocational training campus on the site of the former local wool factory, a large-scale industrial brownfield site. While formally not part of the IUDP, the campus is expected to attract thousands of students and professionals, offering new opportunities for education and employment as well as reshaping the district’s social and economic dynamics. The IUDP builds on this transformation by ensuring that the campus is well integrated into local life – for example through new pedestrian links to the district centre and measures that facilitate broad and inclusive access to its opportunities.

Complementary interventions within the IUDP focus on strengthening the social and cultural infrastructure of the historic centre. The former town hall will be renovated and repurposed as a multifunctional neighbourhood hub, hosting a library, community spaces, and social services to provide low-threshold access to resources and support. The surrounding market square, adjacent streets, and a large public green space will be redesigned to become more attractive, accessible, and inclusive areas for recreation and encounter, encouraging greater use by diverse groups of residents.

To counter widespread vacancy and housing neglect, the programme supports property owners with funding for renovations, energy-efficient upgrades, and heritage-sensitive restoration. In addition, the municipality has acquired several dilapidated housing units for renovation and reallocation as socially managed housing. These measures aim to ensure decent living conditions, reduce housing-related health risks, and prevent segregation and displacement.

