#### IUDP 2 (Bochum)

In Bochum Wattenscheid-Mitte, the IUDP was launched in 2015 with the aim of revitalising the inner-city area of Wattenscheid, a former independent city that became part of Bochum following local government reorganisation in 1975. Wattenscheid was shaped by an active coal mining industry until the mid-1970s and due to structural economic changes is characterised today by a comparatively disadvantaged population. Children in particular show poorer health outcomes at school entry examinations than in other districts of the city, including higher rates of overweight, lower motor skills, and more frequent hearing impairments.

The overall objective of the IUDP is to create a healthier and more family-friendly neighbourhood. The programme combines spatial, social, and physical environmental interventions to address long-standing structural inequalities, with a particular focus on deficits in urban planning and the built environment. Since 2015, several renewal interventions have been completed, including the redesign of parks such as the Friedenspark am Ehrenmal and the Stadtgarten, which now offer diverse functions for play, recreation, and culture. The redesign of Monte-Schlacko – a park located on a former mine dump – is currently underway. Another example of ongoing spatial transformation is the conversion of a former sports field into a multifunctional space for wheel-based active mobility, complemented by tree planting and a rainwater retention basin as part of climate adaptation strategies.

Other interventions include the redesign of playgrounds and schoolyards, as well as the redevelopment of the central square. While the square is both the neighbourhood’s main public transport hub and heavily sealed, making it a recognised heat hotspot in summer, it has long been perceived as lacking comfort and urban quality. Its redevelopment therefore aims to improve both usability and climate resilience, creating a more attractive and comfortable public space for residents. Complementary schemes such as façade improvement grants encourage private investment in the upgrading of residential buildings.

Community funding within the IUDP framework supports a wide range of social and health-related projects. For instance, the annual Health Weeks held each spring provide health-related activities for residents and facilitate networking among local stakeholders.

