#### Ecological sustainability

To assess ecological sustainability, we will draw on multiple data sources. Information on urban green spaces relevant to quality of life and neighbourhood liveability will be collected through on-site inspections conducted by members of the study team. Complementary secondary data on the number and condition of trees within the study areas will be obtained from the respective local authorities. Additional secondary data from these authorities will include information on the proportion of sealed surfaces, which serves as an indicator of the area’s infiltration capacity.

With regard to sustainable mobility, we will assess the share of active mobility in the study areas based on participants’ self-reported usual modes of transport in the survey. Furthermore, we will provide an overview of the neighbourhood conditions that support or hinder active mobility.

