### Data analyses

To evaluate the effectiveness of IUDPs as complex interventions, the intervention areas will be compared with the control areas in regard to the aforementioned evaluation parameters. Regarding the IUDPs’ implementation, this includes an analysis of specific outputs, such as structural or socio-spatial changes in the neighbourhoods. In addition to the assessment of these outputs, we will focus on different outcome parameters in each city: in Bremen (I1, C1), these include Outcomes I and short-term Outcomes II; in Bochum (I2, C2), short- and long-term Outcomes II; and in Wuppertal (I3, C3), long-term Outcomes II and Impacts (Fig. 3).

Both bivariate and multivariate analyses will be conducted using established statistical procedures appropriate to the data structure. Quantitative data from the cross-sectional surveys at two time points, environmental data emerged from the different data collection formats, as well as secondary quantitative data collected at multiple time points, will be analysed using a difference-in-differences (DiD) approach [38]. Both absolute (difference-in-differences) and relative changes (ratio-of-ratios) will be assessed, and inequality effects will be examined through stratification by various social indicators [39]. From an intersectional perspective, social indicators will be selected based on the PROGRESS-Plus framework, as recommended by the Campbell and Cochrane Equity Methods Group [40]. The quantitative data analysis will be carried out using SAS (version 9.4 or higher) and R (version 4.5.1 or higher) [41].

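### Green-space routes appear to take in IUDP-affected sites in intervention areas only, so the area-level contrast can magnify the site-level effect in either direction

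*Protocol article*

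**What the plan says.** All references are to the protocol article.

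- **Assessment of urban green** gives the route rule: "representative circular walking routes that include comparable urban features (e.g., schools, playgrounds, parks) and intervention areas, sites affected by IUDP measures". It then claims: "The approach enables a systematic comparison of urban green quality and its relevance for socio-ecological transformation across all study areas".
- **Study setting** says that in each city "a further district will serve as control area in which no IUDP will be implemented".
- **Data analyses** lists "environmental data emerged from the different data collection formats" among the inputs to the DiD.
- **IUDP 1 (Bremen)** describes work still to come: "The surrounding market square, adjacent streets, and a large public green space will be redesigned".
- **IUDP 2 (Bochum)** reports that since 2015 "several renewal interventions have been completed, including the redesign of parks such as the Friedenspark am Ehrenmal and the Stadtgarten". The same section describes another park redesign as still under way.
- **Ecological sustainability** makes on-site inspection the source for green-space information, and adds data that do not depend on any route: "Complementary secondary data on the number and condition of trees within the study areas will be obtained from the respective local authorities". The share of sealed surface also comes from the authorities.

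**The concern.** The second half of the route rule can be met only where an IUDP exists. Intervention routes would be made of ordinary features plus the places the programme has touched or will touch. Control routes would be made of ordinary features alone, and no matched type of site is named for them. That is a selection rule that depends on the arm, and it sits badly with calling the routes representative of the neighbourhood.

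Ecological sustainability is one of the three dimensions on which the IUDPs are judged. The plant-species indicators in this assessment are not among the municipal data listed under Ecological sustainability. If the walks give extra weight to a few programme sites, a finding about those sites could be reported as a finding about the district. DiD removes fixed level differences between areas. It does not remove extra weight on the places that change between visits.

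**Working it through.** The documents state no figure on this point, so there is none to reproduce. The check has three steps.

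**1. Does the rule differ by arm?** The wording in Assessment of urban green is broken. The likely sense is that routes cover comparable features everywhere and, within intervention areas, also the IUDP-affected sites. Study setting rules out IUDP sites in the control areas. On that reading the rule differs by arm. That the sentence means this is an inference.

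**2. What does this do to an area-level contrast?** Let

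- a = share of the area's green that lies at IUDP sites,
- r = share of the route that lies at IUDP sites,
- d = change at an IUDP site, in SD of a green-quality score, beyond the change at other sites.

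Assume that all other sites change alike in both arms and that the same routes are walked twice. Then

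- true area effect = a × d,
- route-based DiD = r × d,
- bias = (r − a) × d, and ratio = r / a.

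All values below are assumptions chosen to show the range. None comes from the documents.

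| a | r | d (SD) | Area effect a × d | Route result r × d | Ratio |
|---|---|---|---|---|---|
| 10% | 10% | 0.5 | 0.05 | 0.05 | 1 |
| 20% | 30% | 0.5 | 0.10 | 0.15 | 1.5 |
| 10% | 30% | 0.5 | 0.05 | 0.15 | 3 |
| 10% | 50% | 0.5 | 0.05 | 0.25 | 5 |
| 5% | 50% | 0.5 | 0.025 | 0.25 | 10 |
| 10% | 30% | −0.5 | −0.05 | −0.15 | 3 |

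Three things follow.

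- With r = a there is no bias.
- With d = 0 the DiD bias is (r − a) × 0 = 0, so the rule magnifies a site effect but does not create one.
- With d negative, as at a site torn up for construction, the error runs against the intervention.

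A comparison at a single time also picks up any level gap g that the chosen sites already had: bias = (r − a) × g. With a = 10%, r = 30% and g = ±0.5 SD, this is 0.20 × (±0.5) = ±0.10 SD.

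**3. Which areas are exposed?** In Bremen (I1) much of the redesign lies ahead, so site changes may fall between visits and the DiD is exposed. The same holds for Bochum (I2) measures still under way. Measures already completed in Bochum and Wuppertal (I3) are part of the baseline. For them the problem falls mainly on level comparisons.

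**The case against.** The strongest reply has five parts.

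- **The sentence is unclear, and the article is a condensed account.** It does not say how routes are drawn, what share IUDP sites take, or whether they are scored separately. This stands as a limit on certainty. It does not remove the point, because the article states the inclusion rule and the comparative claim side by side.
- **The sites need not be improved ones.** A reader might infer that the routes are drawn through upgraded places and so favour the intervention by construction. The documents do not support that. They speak of sites affected by the IUDP, and the Bremen and Bochum sections show planned and unfinished work. The direction depends on the state of the sites at each visit.
- **The extra weight may be small.** Many IUDP sites are parks, playgrounds and schoolyards, which a feature-based route might pass anyway. This stands: r could be close to a. Even so, certain inclusion in one arm is not the same as inclusion by a common rule.
- **The formula is stylised.** The section describes mapping plant species and conservation status and defines no averaged score. This stands. The table shows how the distortion behaves and does not estimate it, so no particular multiple should be attributed to this study.
- **Visiting IUDP sites serves a stated aim**, namely to see how the programme contributes to socio-ecological transformation. This also stands, and it is a reason to keep those sites, recorded separately.

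**Conclusion.** The point holds in a conditional form. On the most likely reading, the route rule depends on the arm and has no control counterpart, while its data are meant for an area-level comparison and the DiD. If IUDP sites take a larger share of the route than of the area's green, the contrast magnifies the site-level effect. Usually that would overstate benefit once measures succeed, but it would understate benefit while sites are under construction.

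The size cannot be derived from the documents, because neither the shares nor the site effects are given. The conclusion rests on the inferred reading of one garbled sentence and on the route share exceeding the area share. It does not extend to the municipal tree and sealed-surface data, so ecological sustainability as a whole does not hang on it. It is worth correcting before routes are fixed: an analysis plan cannot undo unequal routes afterwards unless the IUDP sites were recorded separately.

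**What to change.** 1. Rewrite the route sentence so that it says plainly which sites are included in which areas.
2. Draw routes in all six areas by one identical rule based on urban features (for example schools, playgrounds, parks), without reference to where IUDP sites lie. Use only these routes for the intervention-versus-control comparison and the DiD. An IUDP site that this rule happens to select stays in.
3. Record IUDP sites as a separate, labelled stratum. Compare them with sites of the same type in the control area, or report them descriptively as outputs.

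The cost is a protocol clarification, some route re-drawing and a few extra assessment points. The air-quality section already selects its sites with GIS by one rule applied in every neighbourhood, so the method is at hand.
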